### Sample size

#### Sample size for severity of depression as primary outcome

In a former RCT on collaborative care performed in the primary care setting, the effect size of a collaborative care intervention versus no such intervention as measured by PHQ-9 was 4.64/7.6 = 0.6 (the SD on the endpoint PHQ-9 varied between 7.0 and 8.3) [104]. In this study, we compare collaborative care plus duloxetine and collaborative care plus placebo versus the monotherapy duloxetine alone, and we compare collaborative care plus duloxetine versus collaborative care plus placebo. To have a minimum power of 80% to detect a standardized difference of 0.5 a minimum of 63 patients per arm is needed, that is 189 completers. In order to anticipate for possible loss to follow up of 20%, 3 × 79 (237) patients will be included [105].

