## Methods/Design

### Objectives

The primary objective of this randomized placebo-controlled trial is to establish effectiveness on severity of depression (measured by Patient Health Questionnaire (PHQ-9)) of a closely monitored integrated intervention (TCCCL + duloxetine) for concomitant depression and (sub)chronic pain compared to either TCCCL + placebo and compared to Duloxetine alone.

Secondary objectives of this trial are to establish cost effectiveness in terms of Quality of Adjusted Life Years (QALY) as measured by EuroQol-5 and SF-36 and costs measured by TIC-P; and to establish improvement on pain in terms of Brief Pain inventory (BPI).

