### The study will evaluate the following hypothesis

#### Hypothesis

Combined treatment (TCCCL + Duloxetine) is more effective than mono-treatment (either TCCCL + placebo or Duloxetine alone) in depressive symptom reduction on the PHQ-9 as main outcome for patients with MDD and (sub) chronic pain.

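### The 80% power at 63 per arm holds for each single comparison; power to show combined treatment superior to both mono-treatments, as the primary hypothesis reads, is about 68–69% at 0.5 SD

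*Protocol article*

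**What the plan says.** The sample size section of the protocol article (Sample size for severity of depression as primary outcome) first lists two comparisons: the two collaborative care arms against duloxetine alone, and the two collaborative care arms against each other. It then gives one calculation: "To have a minimum power of 80% to detect a standardized difference of 0.5 a minimum of 63 patients per arm is needed". This makes 189 completers. It cites an earlier collaborative care trial with an effect of 4.64/7.6 = 0.6. It states no alpha.

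The Hypothesis section contains one hypothesis: "Combined treatment (TCCCL + Duloxetine) is more effective than mono-treatment (either TCCCL + placebo or Duloxetine alone) in depressive symptom reduction on the PHQ-9". The Objectives section sets the combined treatment against two comparators: "compared to either TCCCL + placebo and compared to Duloxetine alone".

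The Analysis section plans two Helmert contrasts: duloxetine alone against the two collaborative care arms, then TCCCL + duloxetine against TCCCL + placebo. No section says whether one or both comparisons must succeed.

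**The concern.** The only power figure for the primary outcome belongs to one comparison, while the only hypothesis on that outcome names two comparators. A reader of these sections together will take 80% as the chance of confirming that combined treatment is better than mono-treatment. If both comparisons must succeed, that chance is lower, and the risk of missing a true 0.5 SD advantage over both comparators is nearer one in three than one in five.

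The planned contrasts add a second difficulty, because neither sets combined treatment directly against duloxetine alone. As the article stands, one significant contrast out of two could be reported as confirming the whole hypothesis.

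**Working it through.** **Inputs.** From the sample size section: standardized difference d = 0.5 (so SD = 1), power 80%, 63 completers in each of three equal arms, and an earlier effect of 0.6. Alpha is assumed to be two-sided 0.05, because that value returns the plan's figure; one-sided 0.05 gives 50 per arm and two-sided 0.025 gives 77.

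**1. The plan's own figure.** For one comparison of two groups, n = 2(1.960 + 0.842)² / 0.5² = 62.8, so 63. This reproduces the plan. The standard error of a pairwise difference is √(2/63) = 0.178, and power = Φ(0.5/0.178 − 1.960) = Φ(0.846) = 80.1%. The t-test version gives 79.5%. The calculation makes no allowance for a second comparison.

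**2. Both pairwise tests.** Write A for TCCCL + duloxetine, B for TCCCL + placebo and C for duloxetine alone, with higher values better. The tests A − B and A − C share arm A, so their correlation is (1/63)/(2/63) = 0.5. Joint power is the bivariate normal probability that both statistics exceed 1.960:

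| True A − B | True A − C | Both succeed |
|---|---|---|
| 0.5 SD | 0.5 SD | 68.9% (about 68% in t-test simulations) |
| 0.5 SD | 0.6 SD | 76% |
| 0.6 SD | 0.6 SD | 86% |

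**3. The planned Helmert contrasts.** The first is (A + B)/2 − C, with standard error √(1/63 + 1/126) = 0.154. The second is A − B, with standard error 0.178. With equal arms they are orthogonal, so in the normal approximation their powers multiply.

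- Combined treatment 0.5 SD better than two equal mono-treatments (A = 0.5, B = C = 0): the first contrast is 0.5/2 = 0.25 SD, with power Φ(0.25/0.154 − 1.960) = Φ(−0.34) = 37%. The second has 80.1%. Jointly 0.367 × 0.801 = 29%.
- Both contrasts truly 0.5 SD: 90.0% × 80.1% = 72.1%. Here A − C = 0.5 + 0.5/2 = 0.75 SD, which is a different and more favourable truth than 0.5 SD over each comparator.

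Because A − C equals the first contrast plus half the second, success on both contrasts would imply that A beats C. That is an indirect and demanding route: it also asks the average of the two collaborative care arms to beat duloxetine alone, which the hypothesis does not require.

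**The case against.** The strongest reply is that the sample size sentence contains no error. It claims at least 80% for a difference of 0.5 SD. The two comparisons listed beside it have 90% and 80% power at that difference, so the minimum is indeed 80%. The sentence does not claim joint power. This stands: a reader might infer a miscalculation, but 63 and 189 both reproduce.

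It can also be said that the trial asks two questions. The Background letters them separately, the Discussion treats them as separate strengths, and the hypothesis uses loose either/or wording. Powering each question is ordinary practice, and a success rule may sit in an analysis plan that is not shown. This stands in part. No rule requiring both is written, and its absence from an article is not the complaint. But the Objectives join the two comparators, and the hypothesis speaks of mono-treatment as a whole, so superiority over both is the plain reading. A later rule requiring both could not turn 80% into the joint power.

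A reader might go further and infer that the design lacks 80% on every reading. The figures do not support that. If both tests must succeed, each keeps 80% at 0.05. If either may succeed with alpha split at 0.025 each, a single test has about 70%, but at least one succeeds in about 85%. Without a split, at least one succeeds in about 91%, but the family-wise error rises to between 9% and 10%.

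Finally, the abstract gives the target as 0.6 SD, and at 0.6 SD in both pairwise tests joint power is 86%. That is true, but the calculation that yields 63 uses 0.5.

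**Conclusion.** The concern holds in a limited form. The 63 per arm and the 80% are right for each comparison. They are not the power for the one stated primary hypothesis, which is about 68–69% when each true difference is 0.5 SD: a shortfall of 11 to 12 points. This rests on an inferred two-sided 0.05, on reading the hypothesis as requiring both comparisons, and on the plan's own 0.5 SD.

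A reader might quote the 72% as the upper end of a single range for confirming the hypothesis. It should not be used that way, because it applies only when both Helmert contrasts are truly 0.5 SD. Under a 0.5 SD advantage over two equal mono-treatments, the planned contrasts jointly succeed in 29%, so the choice of tests matters a good deal.

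**What to change.** In the sample size section, state that 63 completers per arm give 80% power for each single comparison at two-sided 0.05, and about 68–69% power to show superiority over both mono-treatments when each true difference is 0.5 SD.

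In the Analysis section, name the two pairwise tests that address the hypothesis: TCCCL + duloxetine against TCCCL + placebo, and TCCCL + duloxetine against duloxetine alone. The second has to be added, since the planned contrasts do not contain it. State that the hypothesis is confirmed only if both are significant at two-sided 0.05. No alpha adjustment is needed when both must succeed. A single success is reported as that component only, and the Helmert contrasts may stay as supporting analyses.

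The change costs a few sentences and no additional patients. The downside is a less favourable stated power and a stricter claim when only one comparison succeeds. For scale, 80% joint power for the pairwise tests would need 79 completers per arm; the 79 in the plan is the number enrolled per arm before 20% loss.

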**Methods/Design:**

This study is a placebo controlled double blind, three armed randomized multi centre trial. Patients with (sub)chronic pain and a depressive disorder are randomized to either a) collaborative care with duloxetine, b) collaborative care with placebo or c) duloxetine alone. 189 completers are needed to attain sufficient power to show a clinically significant effect of 0.6 SD on the primary outcome measures (PHQ-9 score). Data on depression, anxiety, mental and physical health, medication adherence, medication tolerability, quality of life, patient-doctor relationship, coping, health resource use and productivity will be collected at baseline and after three, six, nine and twelve months.

In the collaborative care conditions a) and b), a care-manager provides Problem Solving Treatment and integrated symptom management guidance with a self-help manual, monitors depressive and pain symptoms, and refers patients to a physiotherapist for treatment according to a 'Graded Activity' protocol. A psychiatrist provides duloxetine or placebo and pain medication according to algorithms, and also monitors pain and depressive symptoms. In condition c), the psychiatrist prescribes duloxetine without collaborative care. After 12 weeks, the patient is referred back to the general practitioner with a consultation letter, with information for further treatment of the patient.

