#### Study design

This study is a three armed randomized Multi Centre trial led by GGz Breburg, with three collaborating mental health institutions: GGz Breburg, Arkin, and GGz inGeest, who will all include 73 patients in order to have 3 × 63 completers for the study. See Figure 1 for treatment options.

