#### Timeframe of the study

The goal is to enroll 219 patients in order to obtain 189 patients that will complete the study. The preparatory period is approximately 6 months. Care-managers will be recruited subsequent to the approval of the Medical Ethical Board and the care-managers will be trained. The inclusion and intervention period will be 24 months. The follow-up phase will last 12 months. Data analysis will take 6 months. The entire study period is 4 years.

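### Enrolment is 237 in the sample size section but 219 elsewhere for the same 189 completers; at the stated 20% loss, 219 gives about 76–77% pairwise power, and the abstract misstates the target effect

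*Protocol article*

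**What the plan says.** The protocol article gives the size of the trial in four places.

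- **Sample size for severity of depression as primary outcome.** The effect and the number of completers are set by "To have a minimum power of 80% to detect a standardized difference of 0.5 a minimum of 63 patients per arm is needed", which makes 189 in all. Enrolment follows: "In order to anticipate for possible loss to follow up of 20%, 3 × 79 (237) patients will be included". The section also reports a standardized effect of 4.64/7.6, rounded to 0.6, from a previous primary care trial of collaborative care.
- **Study design.** The three institutions are described as those "who will all include 73 patients in order to have 3 × 63 completers for the study".
- **Timeframe of the study.** "The goal is to enroll 219 patients in order to obtain 189 patients that will complete the study".
- **Abstract, Methods/Design.** "189 completers are needed to attain sufficient power to show a clinically significant effect of 0.6 SD".

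Only the sample size section states a loss rate. No section states the alpha level or whether the test is one-sided or two-sided.

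**The concern.** All four places share the figure of 189 completers, but they reach it from two enrolment numbers and attach two effect sizes to it. Enrolment cannot be both 237 and 219; the gap is 18 patients. Both sections that describe recruitment, rather than the calculation, use the lower figure, so that is the number the institutions are likely to work to. If loss is 20%, as the sample size section expects, the trial would then fall short of the completers on which its minimum power rests.

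The abstract raises a separate issue. A reader who sees only the abstract would believe that 189 completers are what an effect of 0.6 SD requires. The calculation in the body was made for a smaller effect.

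**Working it through.** **Inputs.** From the sample size section: standardized difference 0.5, power 80%, 63 completers per arm, loss 20%, enrolment 3 × 79 = 237. From Study design and Timeframe: 3 × 73 = 219 enrolled, 189 completers. From the abstract: 0.6 SD. Assumed: two-sided alpha 0.05, because it reproduces 63 per arm (one-sided 0.05 gives 50).

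**1. The plan's own figure.** For two equal arms under the normal approximation, n per arm = 2(1.96 + 0.8416)² / d².

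- At d = 0.5: 2 × 7.849 / 0.25 = 62.8, so 63 per arm and 189 in total. The t-test version gives 64.
- Allowing for 20% loss: 63 / 0.80 = 78.75, so 79 per arm and 3 × 79 = 237.

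The sample size section is therefore internally correct.

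**2. Loss implied by 219.** 1 − 189/219 = 0.137. For comparison, 1 − 189/237 = 0.203. The lower target delivers 189 completers only if no more than 13.7% are lost.

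**3. Pairwise power at 0.5 SD with 20% loss.** Power ≈ Φ(d√(n/2) − 1.96), with the noncentral t as a check. For 219 enrolled, n = 73 × 0.80 = 58.4, so 0.5 × √29.2 − 1.96 = 0.742 and Φ(0.742) = 0.771.

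| Enrolled | Completers per arm | Power, normal | Power, t |
|---|---|---|---|
| 237 | 63.2 | 80.3% | 79.6% |
| 219 | 58.4 | 77.1% | 76.4% |

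Like for like, the loss is about 3 percentage points. If loss were 13.7%, 219 would leave 63 per arm and power of 80.1% (normal) or 79.5% (t).

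**4. The pooled Helmert contrast.** The Analysis section compares duloxetine alone with the two collaborative care arms together. With 58.4 against 116.8 patients, the standard error in SD units is √(1/58.4 + 1/116.8) = 0.160, and Φ(0.5/0.160 − 1.96) is about 0.88 (87.7% normal, 87.3% t). This contrast stays above 80%.

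**5. The 0.6 SD in the abstract.** 2 × 7.849 / 0.36 = 43.6, so 44 per arm (45 by t-test), or 132 to 135 completers. With 63 per arm, power at 0.6 SD is 92.0% (normal) or 91.6% (t). With 58.4 per arm it is 90.0% or 89.5%. So 189 completers is not what 0.6 SD requires at 80% power; it is what 0.5 SD requires.

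**The case against.** The strongest reply is that this is a bookkeeping discrepancy with a small effect. Much of that stands.

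- The shortfall is about 3 points. It depends on the full 20% being lost and applies only to two-arm comparisons.
- A reader might infer that three separate contradictions each erode power. The documents do not support that. There is one enrolment conflict; 13.7% is only its arithmetic consequence, not a second stated loss rate. The 0.5 versus 0.6 mismatch reduces nothing, since sizing on 0.5 is the more cautious choice.
- A reader might infer that the whole trial is underpowered. The pooled contrast is not.
- A reader might infer that the Study design section confuses patients per institution with patients per arm. There are three of each, and 3 × 63 can be read either way with the same totals, so this adds no error.
- A reader might infer that recruitment will stop at 73 per institution. The Timeframe section calls 219 a goal, and nothing makes it a cap.

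What does not stand is the suggestion that the discrepancy can be left. The affected contrast, TCCCL + duloxetine versus TCCCL + placebo, is one of the two in the Analysis section, and the Hypothesis section sets combined treatment against each monotherapy. Nor can a lower loss simply be presumed. The Analysis section also removes non-compliant and emergency-deblinded patients, and no rate is given for them. Purely as an illustration, total losses of 25% and 30% from 219 would give pairwise power of about 74% and 71%.

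**Conclusion.** The point holds in a limited form. The protocol states two enrolment targets for the same 189 completers, and the lower one does not meet its minimum power of 80% under its own 20% loss: pairwise power at 0.5 SD is about 76% (t) or 77% (normal). This rests on two-sided alpha 0.05, equal arms, loss spread evenly over the arms, and an unadjusted two-group comparison. It concerns two-arm comparisons only.

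The effect size in the abstract is a separate misstatement. It gives 0.6 SD, the effect from the previous trial, as the basis for a number derived from 0.5 SD. It should be corrected because it misinforms the reader, not because it weakens the trial.

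The documents do not show which enrolment figure is operative, so the finding is that they must be reconciled, not that 219 is necessarily the wrong one.

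**What to change.** Bring the abstract, Study design, Sample size and Timeframe sections to one set of numbers, by one of two routes.

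- **Adopt 237.** Replace 73 per institution with 79 (if recruitment is split equally) and 219 with 237. The sample size section then stands as written. This costs a text change and 18 more patients than the lower target.
- **Keep 219.** Amend the sample size section to 219 and either restate pairwise power at 0.5 SD as about 76–77% with 20% loss, or replace the 20% with an allowance of about 14% and give a reason for it. The cost is a less favourable power statement or the need to defend a lower loss.

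Under either route, change the abstract to 0.5 SD, keep 0.6 only as the effect seen in the previous trial, and state the alpha level and sidedness behind the 63 per arm.

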### Emergency deblinding

Emergency deblinding of the medication condition is performed by telephone to a research associate who is not involved in treatment procedures. This happens in case of serious adverse medical events. Subjects, who are deblinded before the end of the treatment procedures, will not be incorporated in the final analysis. In case of emergency deblinding or non-compliance, the code of medication (duloxetine or placebo) in the collaborative care groups will be broken. In case of duloxetine, the medication will be reduced and stopped according to protocol. All the remaining medication of this patient will be asked back and stored in a closed cabinet, separately from the rest of the study medication. In case of non-compliance, the patient will be excluded from this study and the final analysis.

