### Exclusion of the study during the intervention phase

Non-compliance is defined as not having used at least 80% of the prescribed medication (duloxetine/placebo) or no show on more than 20% of the appointments made with the psychiatrist or care-manager. The psychiatrist uses pill counts at every session to check if at least 80% of the pills have been used.

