#### Analysis

Apart from patients that will have to be excluded because of noncompliance as described above, or patients who had to undergo emergency deblinding due to serious medical adverse events, intention to treat analysis will be performed. Multi Level Analysis will be performed which will allow us to correct for variance associated with the different sites in this Multisite RCT. Effect sizes will be estimated in terms of Cohen's d and regression analysis will be performed. Possible confounders such as age, gender, immigrant status, level of education, history of treatment and life events will be included as covariates in the analysis. An independent Helmert analysis will be performed with the following contrasts: Duloxetine alone versus TCCCL + duloxetine and TCCCL + placebo; and then TCCCL + duloxetine versus TCCCL plus placebo.

To assess the cost effectiveness, we will apply a cost-utility analysis. The results will be expressed as cost per QALY. The economic evaluation will be undertaken from a societal perspective. Hence, all relevant effects and costs due to resource utilisation within the healthcare (direct medical costs) and costs due to production losses (productivity costs) will be included.

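### The 20% enrolment allowance is spent on loss to follow-up alone, so if the planned non-compliance and deblinding exclusions come on top of it, 63 analysed per arm and 80% power are not assured for the 1:1 comparisons

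*Protocol article*

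**What the plan says.** The protocol article's sample size section sets its target as follows: "To have a minimum power of 80% to detect a standardized difference of 0.5". For that target it asks for 63 in each arm, 189 in total, and counts these as patients who complete the study. It then names one route of loss, "In order to anticipate for possible loss to follow up of 20"%, and arrives at 79 per arm, 237 in total.

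Three other sections open further routes out of the analysis:

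- Emergency deblinding: "In case of non-compliance, the patient will be excluded from this study and the final analysis". The same section also leaves out of the final analysis anyone deblinded before treatment ends.
- Exclusion of the study during the intervention phase: "Non-compliance is defined as not having used at least 80% of the prescribed medication", or alternatively missing more than 20% of appointments with the psychiatrist or care-manager. Pills are counted at every psychiatrist session.
- Analysis: the intention-to-treat analysis is qualified by "Apart from patients that will have to be excluded because of noncompliance as described above, or patients who had to undergo emergency deblinding" for serious adverse events.

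The document gives no expected rate for either exclusion. It does not say whether such patients count within the 20%.

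**The concern.** The step from 63 to 79 covers one loss route, while the analysis rules create two more. A patient can take fewer than 80% of the capsules, or miss more than a fifth of appointments, and still return every questionnaire up to twelve months. That patient is not lost to follow-up but is dropped from the analysis. The allowance as labelled does not cover this patient.

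The stake is how a null result would be read. The comparison of TCCCL + duloxetine with TCCCL + placebo is the only blinded one, the second Helmert contrast and part of the stated hypothesis. The hypothesis also compares TCCCL + duloxetine with duloxetine alone, again 1:1. If either came out null, it would be judged against 80% power that the analysed numbers may not support.

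This is separate from the conflict between 237 enrolled (sample size section) and 219 enrolled (timeframe section; three centres of 73 in the study design section). The point remains if 237 is adopted. It is also separate from the bias that post-randomisation exclusions can cause.

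**Working it through.** **Inputs.** Difference 0.5 SD, power 80%, 63 per arm, 20% loss, 79 per arm and 237 in total (sample size section); contrasts from the Analysis section. Alpha is not stated. I assume 0.05 two-sided because it reproduces 63; one-sided 0.05 gives 50.

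**1. Reproduce the plan's figures.**

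- n per arm = 2(z₀.₉₇₅ + z₀.₈₀)² / d² = 2(1.960 + 0.842)² / 0.25 = 62.8, rounded up to 63.
- Enrolment = 63 / (1 − 0.20) = 78.75, rounded up to 79 per arm; 3 × 79 = 237.

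All the figures reproduce. By the exact noncentral t calculation, 63 per arm gives 79.5%, against 80.1% by the normal approximation. So 79.5% is the right baseline for the powers below.

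**2. Reserve in the allowance.** 79 × 0.8 = 63.2. Total attrition by every route can be at most 79 − 63 = 16 per arm, or 16/79 = 20.3%. If loss to follow-up alone reaches 20%, any additional exclusion takes the arm below 63.

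**3. Effect of additional exclusions.** Let x be the share of followed-up patients who are then excluded. The document gives no x, so the range is assumed, and it is taken as equal in all arms.

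- Analysed n per arm = 79 × 0.8 × (1 − x).
- 1:1 comparison: two-sided 5% t-test, noncentrality 0.5 × √(n/2).
- 1:2 Helmert contrast (duloxetine alone versus both TCCCL arms, n against 2n): noncentrality 0.5 × √(2n/3).

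| x | Analysed n per arm | Power, 1:1 | Power, 1:2 |
|---|---|---|---|
| 0 | 63.2 | 79.6% | 89.8% |
| 5% | 60.0 | 77.6% | 88.2% |
| 10% | 56.9 | 75.3% | 86.5% |
| 15% | 53.7 | 72.8% | 84.5% |
| 20% | 50.6 | 70.2% | 82.2% |

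Losing a single patient per arm (63 to 62) moves the 1:1 power from 79.5% to 78.9%.

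**4. Enrolment that would hold 63 analysed.** 63 / [0.8(1 − x)] gives 83, 88, 93 or 99 per arm at x = 5%, 10%, 15% or 20%. This shows the scale only; the fix does not depend on it.

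**The case against.** A reader might infer that 237 enrolled cannot yield 63 analysed per arm, or that the trial as a whole is underpowered. The document supports neither.

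- **The shortfall is conditional.** It requires loss to reach the full 20%, which the section calls only possible, and exclusions that add to that loss. A non-compliant patient is removed from the study as well as from the analysis, so could be counted as a non-completer within the step from 237 to 189. Repeated no-shows and dropout probably overlap. Up to 16 of 79 per arm may leave by any route and 63 still remain. This objection stands in full, and it is why the conclusion is that 63 is not assured.
- **One of the two planned contrasts is hardly affected.** The 1:2 contrast keeps about 82% at the far end of the range. This also stands, so the point is confined to the 1:1 comparisons.
- **At the low end the loss is small.** With a further 5% excluded, the 1:1 power drops about two points. Half a point of the gap to 80% comes from the normal approximation and not from the exclusions.
- **Equal exclusion across arms is a simplification.** Emergency code-breaking concerns only the two blinded arms.
- **The abstract names a larger effect:** "189 completers are needed to attain sufficient power to show a clinically significant effect of 0.6 SD". At 0.6 SD the same formula needs only 2 × 7.849 / 0.36 = 43.6, so 44 per arm, and the shortfall would not matter over this range. The sample size section, however, ties 63 and 80% to 0.5 SD, and its claim has to be judged on that value.

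What remains is the mismatch itself. The protocol fixes both the allowance and the exclusions, and the one takes no account of the other. A separate analysis plan would not cure that.

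**Conclusion.** The point holds in a limited form. None of the plan's arithmetic is wrong. What is wrong as written is the unqualified power statement: it does not allow for exclusions that the plan's own analysis rules impose, and the inflation leaves no room for them.

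If the exclusions are additional to a 20% loss, power at 0.5 SD for the 1:1 comparisons falls from 79.5% to about 78%, 75%, 73% or 70% as a further 5%, 10%, 15% or 20% are removed. These figures rest on an assumed two-sided 5% t-test, 237 enrolled, a full 20% loss, no overlap between loss and exclusion, and equal exclusion rates across arms. If the routes overlap, or loss falls below 20%, the effect is smaller and may vanish. The 1:2 contrast stays above 80% throughout, so no general claim of inadequate power follows.

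**What to change.** Preferred: in the Analysis section, keep every randomised patient with outcome data in the primary PHQ-9 analysis, whatever their compliance or deblinding status, and bring the exclusion sentences under Emergency deblinding into line. The exclusions then no longer reduce the analysed number, and the 20% allowance and the 237 stand as written. Patients who leave study treatment must still be sent the outcome questionnaires; rules on stopping study medication need not change. The compliance-based set can be kept as a secondary analysis.

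Otherwise, state an expected exclusion rate in the sample size section, say whether it is additional to the 20%, and restate the analysed number and the power for the 1:1 comparisons. For example, a further 10% excluded gives about 57 per arm and 75%. Relabelling the 20% as covering every route, without a reason to expect total attrition that low, would not make the 80% any better assured.

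The cost is a few sentences and, on the second route, one recalculated figure and a slightly less favourable power statement. No extra enrolment is needed on either route.
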